### Randomization and Blinding

Participants are randomly assigned in a 1:1 ratio to the intervention or control group using a block randomization approach with stratification by ward seniority (junior vs senior nurses). Allocation concealment is ensured using sequentially numbered, opaque, sealed envelopes prepared independently before enrollment. Blinding of participants is not feasible due to the nature of the educational intervention. However, outcome assessors and data analysts remain blinded to group allocation. To reduce contamination, training sessions are conducted during off-duty hours, intervention materials are restricted to the intervention group, and patient allocation is organized after completion of training. The control group is offered access to the CCCM after study completion.

### Study Phases

#### Phase 1

The CCCM was developed using a qualitative exploratory design. In-depth interviews were conducted with registered nurses, nurse educators, sociologists, psychologists, and patients from diverse cultural backgrounds (Multimedia Appendix 2). The interviews explored communication barriers, culturally sensitive practices, and sociocultural considerations in care delivery. Data were analyzed using Braun and Clarke’s [17] 6-step thematic analysis framework. Emergent themes informed the structure, learning objectives, and content domains of the CCCM.

#### Phase 2

Validation of the CCCM and patient satisfaction tool: the CCCM and a culturally sensitive patient satisfaction tool were validated using a 2-round Delphi process involving experts in transcultural nursing and health care communication. Content validity was assessed in terms of relevance, clarity, and applicability. The CCCM achieved a content validity index (CVI) of ≥0.89. Revisions were incorporated based on expert feedback.

Phases 1 and 2 of the study are completed. Phase 3 is planned as per the following details.

#### Phase 3

RCT: participants are randomized to either the intervention group (CCCM plus routine care) or the control group (routine care only). The effectiveness of the intervention is assessed through comparison of outcomes between groups.

### Intervention

The CCCM is a structured educational intervention designed to improve cultural competence among nurses. It is delivered as five 1-hour sessions over 5 consecutive days, followed by booster sessions on days 15, 35, and 45. The module includes components on cultural self-awareness (guided by the ASKED [awareness, skills, knowledge, encounter, desire] framework), cross-language communication, religious and end-of-life care, and sociocultural considerations in the Indian context. It also incorporates elements of leadership and advocacy in culturally responsive practice. The components of the CCCM were systematically mapped to established cultural competence frameworks to ensure theoretical grounding and comprehensiveness, as shown in Table 1.

A blended learning approach is used, combining didactic teaching with experiential methods such as simulation, role-play, and case-based discussions. Participants are required to attend at least 80% of sessions to be considered compliant. The control group continues routine nursing care without exposure to the CCCM during the study period.

**Table 1 table1:** Mapping of culturally competent care module (CCCM) components to cultural competence frameworks.

CCCM session component and Campinha-Bacote [2] domains			Purnell [13] domains		Giger and Davidhizar [12] phenomena
Cultural self-awareness (ASKED^a^ framework)					
	Cultural awareness	Overview or heritage		Social organization	
	Cultural desire	Workforce issues		Environmental control	
Cross-language communication strategies					
	Cultural skill	Communication		Communication	
	Cultural encounters	Health care practices		Space	
Religious and end-of-life considerations					
	Cultural knowledge	Spirituality		Social organization	
	Cultural skill	Death rituals		Time orientation	
India-specific sociocultural adaptations					
	Cultural knowledge	Family roles		Social organization	
	Cultural encounters	Biocultural ecology		Biological variations	
Leadership and advocacy in culturally responsive care					
	Cultural desire	Health care organization		Environmental control	
	Cultural encounters	Workforce issues		Social organization	
Simulation-based role-play					
	Cultural skill	Multiple integrated domains		Communication	
	Cultural encounters	Multiple integrated domains		Time	
	Cultural encounters	Multiple integrated domains		Social organization	

^a^ASKED: awareness, skills, knowledge, encounter, desire.

### Outcomes

The primary outcome is cultural competence, measured using the CCAT-N, a validated instrument that provides a total score reflecting overall cultural competence. Secondary outcomes include domain-specific subscale scores of cultural competence, patient satisfaction, and retention of cultural competence at 90 days following the intervention. Higher scores on these measures indicate improved outcomes.

### Data Collection

Data are collected at 3 time points: baseline (before the randomization), immediately after completion of the intervention, and at 90 days after the intervention to assess retention. The schedule of enrollment, intervention, and outcome assessments is presented in Table 2.

Cultural competence is assessed using the CCAT-N, while patient satisfaction is measured using a culturally competent nursing care satisfaction survey. Standardized data collection procedures are followed across all time points to ensure consistency and reduce measurement bias.

**Table 2 table2:** Schedule of enrollment, interventions, and assessments (SPIRIT [Standard Protocol Items: Recommendations for Interventional Trials] format).

Study component	Baseline (t-1)	Allocation (0)	Weeks 1-2	Week 3	Day 90
Enrollment procedures					
Eligibility screening	✓				
Informed consent	✓				
Baseline demographic data	✓				
Baseline cultural competence (CCAT-N^a^)	✓				
Randomization		✓			
Intervention group (CCCM^b^)					
5 structured CCCM sessions			✓		
Booster reinforcement activities			✓	✓	
Control group					
Routine ward training			✓		
Outcome assessments					
Cultural competence (CCAT-N)	✓			✓	✓
Patient satisfaction survey				✓	✓
Process evaluation checklist			✓	✓	
Adverse event monitoring			✓	✓	✓

^a^CCAT-N: Cultural Competence Assessment Tool for Nurses.

^b^CCCM: culturally competent care module.

### Data Analysis

Data analysis is conducted to compare outcomes between the intervention and control groups. Descriptive statistics are used to summarize baseline characteristics and outcome variables. Baseline comparability between groups is assessed prior to outcome analysis. For the primary outcome, postintervention CCAT-N scores are compared between groups using a 2-tailed independent samples *t* test. Where baseline differences are present, analysis of covariance is applied to adjust for baseline values. Changes in outcomes over time are analyzed using repeated measures analysis of variance or mixed-effects modeling to account for within-participants variability. Both intention-to-treat and per-protocol analyses are performed to ensure robustness of findings. Missing data are addressed using multiple imputation methods. For patient satisfaction outcomes, either parametric or nonparametric statistical tests are applied depending on data distribution. Subgroup analyses are conducted to explore potential effect modification based on ward seniority. A 2-tailed *P* value of <.05 is considered statistically significant.

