**Methods:**

This 3-phase parallel-group RCT is being conducted in the medical-surgical wards of the Acharya Vinoba Bhave Rural Hospital, Wardha, Maharashtra, India (2024-2026). In phase 1 (completed), the CCCM was developed via thematic analysis of 20 interviews with nurses, educators, and patients. In phase 2 (completed), the CCCM and a patient satisfaction tool were validated using a 2-round Delphi process involving 15 experts (CCCM: content validity index ≥0.89; patient satisfaction tool: Cronbach α=0.87-0.92). Phase 3 is ongoing: 55 nurses are randomized in a 1:1 ratio to either the CCCM (5×1-hour sessions+boosters) or routine care. The primary outcome is the postintervention Cultural Competence Assessment Tool for Nurses score, while secondary outcomes include subscales, patient satisfaction, and 90-day retention. The sample size is calculated using G*Power based on an anticipated effect size of 0.82. Participants are randomly allocated through computer-generated block randomization stratified by seniority, and outcome assessors and data analysts are blinded to group allocation. Data will be analyzed using SPSS (intention-to-treat, linear mixed-effects models; *P*<.05). Patient satisfaction outcomes will be evaluated using data from 120 patients.

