### Study Setting

The trial is being conducted in 6 independent medical-surgical wards of the Acharya Vinoba Bhave Rural Hospital, a tertiary care teaching hospital serving a culturally and socioeconomically diverse population from rural and semiurban regions of Maharashtra. Each ward is staffed by 2 to 3 registered nurses per shift, which supports individual randomization while reducing the risk of contamination between study groups.

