### Sample Size Determination

The sample size is calculated based on the primary outcome of cultural competence measured using the CCAT-N. Pilot data indicated a large effect size (Cohen *d*≈0.8). Assuming a 2-tailed significance level of .05 and a statistical power of 90%, a minimum of 34 participants per group is required. After accounting for a potential attrition rate of 20%, the final sample size is set at 55 participants per group, resulting in a total of 110 nurses.

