### Planned Data Analysis

Quantitative analysis for phase 3 will focus on evaluating the effectiveness of the CCCM intervention. The primary outcome, namely, cultural competence as measured by total CCAT-N scores, will be analyzed using linear mixed-effects models, incorporating random intercepts to account for clustering at the ward level.

Secondary outcomes will be analyzed using generalized estimating equations to assess changes over time across baseline, postintervention, and 90-day follow-up measurements. Mediation analysis will also be conducted to examine whether improvements in cultural competence mediate changes in patient satisfaction.

Missing data will be handled using multiple imputation methods, provided that missingness does not exceed 20%, and patterns of missing data will be carefully examined prior to analysis.

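### Patient satisfaction has two conflicting analyses, neither clustered on the randomized nurse, and no rule ties a patient to one nurse or arm

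*Protocol article*

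**What the plan says.** Two sections of the protocol article prescribe an analysis for the same outcome.

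- Methods, Data Analysis: "For patient satisfaction outcomes, either parametric or nonparametric statistical tests are applied depending on data distribution". No nurse or ward term is named.
- Results, Planned Data Analysis: "Secondary outcomes will be analyzed using generalized estimating equations to assess changes over time across baseline, postintervention, and 90-day follow-up measurements". The Outcomes section puts satisfaction in that group: "Secondary outcomes include domain-specific subscale scores of cultural competence, patient satisfaction, and retention of cultural competence at 90 days following the intervention". The GEE cluster unit is not named. The ward random intercept in the same section ("incorporating random intercepts to account for clustering at the ward level") belongs to the primary CCAT-N model.

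Table 2 schedules the satisfaction survey at Week 3 and Day 90 only.

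On design, nurses are allocated individually ("resulting in a total of 110 nurses", 55 per arm), stratified by seniority and not by ward, in six wards. Study Setting adds: "Each ward is staffed by 2 to 3 registered nurses per shift, which supports individual randomization while reducing the risk of contamination". On patients, the Abstract says: "Patient satisfaction outcomes will be evaluated using data from 120 patients". Randomization and Blinding says only that "patient allocation is organized after completion of training". Planned Data Analysis also announces a mediation analysis from nurses' cultural competence to patient satisfaction.

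**The concern.** Three things are at stake.

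1. **Which analysis counts.** A test picked after looking at the distribution and a longitudinal GEE can give different answers, and they need not estimate the same quantity: a rank test does not compare means. With both in the text, the choice stays open until the data are seen. The GEE as described also cannot be run for satisfaction, because it includes a baseline measurement that Table 2 does not schedule.
2. **The unit of inference.** The nurse is randomized and the patient is measured. Where several patients share a nurse, their answers are correlated, and a test that ignores this gives standard errors that are too small.
3. **What a patient's arm means.** Patients are not randomized, so a patient has an arm only through a nurse. Without a stated link the arm comparison is not defined, and the mediation analysis has no nurse score to attach to a patient. If a patient is nursed by both arms, the label captures only part of the exposure and the contrast shrinks.

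**Working it through.** **The plan's own figure.** The only number for this outcome is 120 patients. The article gives no effect size, power or intracluster correlation (ICC) for it, so it cannot be reproduced. The checks below ask what follows from 120 patients and 110 nurses.

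**Check 1: do the two statements agree?**

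| | Data Analysis | Planned Data Analysis |
|---|---|---|
| Method | Parametric or nonparametric test, chosen by distribution | GEE |
| Time points | Not stated | Baseline, postintervention, day 90 |
| Fits Table 2 for satisfaction? | Yes, at either wave | No, there is no baseline survey |
| Cluster unit | None named | None named |

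They do not agree, and neither names the nurse.

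**Check 2: cost of ignoring nurse clustering.**

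- From the documents: 120 patients, 110 nurses, two-sided alpha 0.05.
- Assumed: ICC 0.05 to 0.10; equal numbers of patients (m) per contributing nurse; each patient attributed to one nurse.
- Formulas: DE = 1 + (m − 1) × ICC; true alpha = 2 × [1 − Φ(1.96/√DE)].

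| Nurses contributing | m = 120/nurses | DE, ICC 0.05 | DE, ICC 0.10 | True alpha |
|---|---|---|---|---|
| 110 | 1.09 | 1.005 | 1.009 | 5.1% at both |
| 60 | 2 | 1.05 | 1.10 | 5.6% to 6.2% |
| 30 | 4 | 1.15 | 1.30 | 6.8% to 8.6% |
| 12 | 10 | 1.45 | 1.90 | 10.4% to 15.5% |

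Example, 30 nurses and ICC 0.10: DE = 1 + 3 × 0.10 = 1.30; 1.96/√1.30 = 1.72; true alpha = 8.6%. With all 110 nurses contributing, even ICC 0.20 gives DE 1.018 and a true alpha of 5.2%.

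**Check 3: is mixed-arm care plausible?** 110/6 is about 18 nurses per ward, and allocation is not stratified by ward, so both arms can be expected in each ward. If the nurses on a shift are drawn without regard to arm, the chance that all are of one arm is 2 × C(55,s)/C(110,s): about 50% for s = 2 and 24% for s = 3. This describes who is on the ward, not who nurses a given patient.

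**Illustration of dilution, on assumed inputs only.** Suppose 60 patients per arm, a standardized effect of 0.5, and a share c of each patient's care given by the other arm. The effect becomes 0.5 × (1 − 2c), and power = Φ[effect × √(60/2) − 1.96].

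- c = 0: power 0.78
- c = 0.10: effect 0.40, power 0.59
- c = 0.25: effect 0.25, power 0.28

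The documents give neither c nor the effect size.

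**The case against.** The case on the other side is substantial.

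- **GEE is a method for correlated data, and the plan names it.** This stands. A reader of the Data Analysis section alone might infer that satisfaction will be compared only by two-sample tests that take patients as independent. The documents do not support that: the wording does not say two-sample or independent, and the other section names GEE. What remains is a conflict, with the cluster unit unnamed in both places.
- **The average is about 1.1 patients per nurse.** This also stands. At that spread the inflation is negligible. Nothing in the article secures an even spread, but nothing says that a few nurses supply most patients either.
- **Mixed-arm care is not stated.** A reader might infer from the shared wards and shifts that most patients are nursed by both arms. The documents do not establish this. Patient allocation after training is listed among the contamination controls, and its mechanism may be set out in the full protocol. Any probability that a patient stays within one arm over several shifts would need continuity of assignment and length of stay, which are not given.
- **The two harms pull against each other.** The design effect takes each patient as belonging to one nurse; dilution takes care as shared. Both cannot apply at full strength.
- **Ward correlation.** With arms mixed within wards, shared ward effects largely cancel in the arm contrast, so the point about standard errors concerns nurses, not wards.
- **Analysis wording cannot undo dilution,** which is a feature of the design. Agreed; a roster-based analysis can only show how far it may have gone.

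**Conclusion.** The concern holds as a conflict and a missing link. Two sections give incompatible analyses for patient satisfaction, one of which calls for a baseline that the schedule lacks. Neither clusters on the randomized nurse, and no rule attaches a patient to a nurse or arm, although two planned analyses depend on one.

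The effect on type I error is conditional: 6.8% to 8.6% at 4 patients per nurse with an assumed ICC of 0.05 to 0.10, and about 5.1% if the patients spread evenly over all nurses. A reader might conclude that the error rate is known to be inflated; at the only average the documents imply, it is not. Dilution through mixed-arm care is plausible, but its size cannot be derived from the documents.

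Severity is moderate. Satisfaction is a secondary outcome, and the primary CCAT-N comparison is not affected by this point. Satisfaction does, however, appear in the study objective, the hypothesis and the conclusions, so its analysis should be settled before the final analysis due by June 2026.

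**What to change.** 1. Delete the distribution-dependent test from Data Analysis and state one analysis in both sections: either a linear mixed model with a random intercept for the index nurse, or GEE with robust errors clustered on the index nurse. With about 1.1 patients per nurse a nurse intercept may be barely identifiable, which favours GEE. Covariates: arm, survey wave (Week 3 or Day 90), seniority and ward.
2. Include no baseline term, since none is collected.
3. State whether the same patients answer at both waves and, if so, add a patient-level term.
4. State the rule that links each patient to an index nurse, and use the same link in the mediation analysis. If the full protocol already holds the rule, cite it.
5. Where duty rosters allow, add the share of each patient's care given by CCCM-trained nurses as a sensitivity analysis.

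The cost is a change of wording, a roster look-up and slightly wider confidence intervals. No new patients are needed. The real limit is timing: 92 of the 120 patients (77%) were already enrolled, and if the index nurse was not recorded for some of them the link may not be recoverable. The number of unlinked patients should then be reported.

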### Data Management

All data are stored in secure, encrypted institutional databases. Double-entry verification is used to ensure accuracy. Data quality is monitored regularly, and an audit trail is maintained throughout the study.

### Ethical Considerations

Ethics approval was obtained from the Datta Meghe Institute of Higher Education & Research Institutional Ethics Committee (DMIHER-DU/IEC/2024/52; December 20, 2024). The trial is registered with the Clinical Trial Registry of India (CTRI/2025/06/088982; May 17, 2025). The study involves minimal risk, as it is an educational intervention. Written informed consent will be obtained from all participants prior to enrollment. Participants will be informed of their right to withdraw at any time without penalty. No formal data monitoring committee has been constituted due to the low-risk nature of the study. The study adheres to the Declaration of Helsinki principles, protecting participants’ rights, privacy, and confidentiality.

## Results

### Trial Status and Progress (Updated February 13, 2026)

#### Phase 1: Development of the CCCM

Phase 1 of the study, which was conducted between March and April 2025, focused on the development of the CCCM. The module was developed using a qualitative approach guided by reflexive thematic analysis, as described by Braun and Clarke [17]. This approach emphasized researcher reflexivity, with the principal investigator maintaining a reflexive journal to document positionality and potential cultural biases throughout the analytical process.

A total of 20 in-depth interviews, each lasting 45 to 60 minutes, were conducted with registered nurses, nurse educators, and patients from diverse cultural backgrounds. Data were analyzed through iterative coding and theme development, resulting in the identification of 5 key domains that informed the structure and content of the CCCM. To ensure methodological rigor, multiple strategies were used. Credibility was enhanced through member checking, while dependability was ensured maintaining a comprehensive audit trail. Confirmability was supported through peer debriefing, and transferability was addressed through detailed contextual descriptions of the study setting and participants.

#### Phase 2: Validation of the CCCM and Study Instruments

Phase 2, conducted between June and July 2025, involved the validation of the CCCM and the culturally adapted patient satisfaction tool. Content validation was performed using a 2-round modified Delphi technique involving 15 experts, including sociologists (n=2), psychologist (n=1) physician (n=1), nurse educators (n=8), and clinical nursing leaders (n=3).

The CCCM achieved a CVI of 0.89, while the patient satisfaction tool demonstrated a CVI of 0.92, indicating high agreement among experts regarding relevance and clarity. The CCAT-N, adapted for this study, demonstrated strong psychometric properties. Internal consistency was high (Cronbach α=0.87), and test-retest reliability over a 14-day interval was satisfactory (*r*=0.82). The tool also showed good sensitivity to change, with a pilot study indicating a large effect size (Cohen *d*=0.82). The 15-item patient satisfaction tool, measured on a 5-point Likert scale, demonstrated high internal consistency (Cronbach α=0.89). Construct validity was established through exploratory factor analysis, which identified 2 primary factors accounting for 73% of the total variance, namely, “respect for cultural practices” (42%) and “effective communication” (31%).

#### Phase 3: RCT Implementation Status

Phase 3 of the study is currently in progress. Participant recruitment commenced in August 2025. As of February 2026, a total of 110 participants have been enrolled and randomized, representing 100% of the target sample size. Participants have been equally allocated to the intervention group (n=55) and the control group (n=55).

Baseline data collection was completed between August and October 2025. The CCCM intervention was delivered to the intervention group between October and November 2025, following which immediate postintervention assessments were conducted in November 2025.

Follow-up assessments at 90 days after the intervention are currently underway and are expected to be completed between February and March 2026. Final data analysis is anticipated to be completed by June 2026.

